#### Additional outcomes

Additional multiple outcomes are the results obtained during the intervention itself (i.e. HR, online and offline questionnaires), in addition to the TDMS scale results.

### Sample size

Considering that the main outcome of this study is the RT of the Stroop task (which is claimed by many to be one of the indicators of executive performance), which typically has a moderate effect, we calculated a sample size of 28 individuals (with α error probability set at 0.05 and power set at 0.8). We decided to recruit 30 participants to eventually control for drop-off.

### Data management

Every participant will be assigned a code according to their arrival at the laboratory to attend the first session, independently from the intervention condition (S01, S02, etc.). Personal information and data for this experiment are handled exclusively by the involved researchers (Tohoku University). According to the institutional policy [56], in order to ensure the security of all data and personal information, it is limited to the involved researchers (and to external parts only after their formal approval). After the end of the experimental period, any information directly linking data back to the participant will be discarded to guarantee anonymity. Personal data eventually collected will not be shared or disclosed in any way.

### Statistical analysis

The current RCT is designed to determine whether a virtual intervention has a beneficial effect on executive functions; this is possible only if some assumptions, during the intervention itself, are satisfied (e.g. embodiment over the virtual body in 1PP). Consequently, the data analysis will be organized in two phases: in the first phase, the results collected during the intervention itself will be checked (i.e. HR, online and offline questionnaires) in order to see whether the virtual intervention is actually effective. In the second phase, the measurements will be analyzed to check the hypothesis (i.e. Stroop task and fNIRS data) and their correlations.

#### Heart rate data

For the HR, the data of the three recording periods (baseline, running, and slow walking) for 4 min each will be averaged: the averaged baseline (HRb) results will be subtracted by the averaged running (HRr) and the averaged walking (HRw) results:
$$ \mathrm{dHRr}=\left(\mathrm{HRr}-\mathrm{HRb}\right);\mathrm{dHRw}=\left(\mathrm{HRw}-\mathrm{HRb}\right) $$

Then, an ANOVA 2 × 2 with factor HR speed at two levels (dHRr = fast, dHRw = slow) and factor CONDITION at two levels corresponding to the intervention conditions (1PP, 3PP) will be run. We predict finding a significant increase in the dHRr in the 1PP condition, with respect to all the other measurements, in order to confirm the physiological counterpart of the embodiment of the virtual body in 1PP only.

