**Methods:**

In a cross-over randomized controlled trial, 30 healthy young adults will experience HIE training in IVR (i.e. the virtual body will perform eight sets of 30 s of running followed by 30 s of slow walking, while the participant is completely still) according to two random-ordered conditions: during the experimental condition, the virtual body is displayed in first-person perspective (1PP), while in the control condition, the virtual body is displayed in third-person perspective (3PP). To confirm that individuals have the illusion of ownership and agency over the virtual body in 1PP (and not in 3PP), we will record the heart rate, in addition to subjective questionnaires. Before and after every IVR sessions (one week apart), we will measure cortical hemodynamic changes in the participants’ prefrontal cortex using the fNIRS device during the Stroop task’s execution.

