After that, the actual intervention consists of a vHIE performed by the virtual body exclusively: while seated, participants will see the virtual body (either in 1PP or 3PP) alternating 30 s of running and 30 s of slow walking, for a total of 8 min [17, 33]. After that, we will ask the participant to stay still and close his/her eyes, while we still record an extra 30 s of the HR (see the “Measurements” section) (see Fig. 2b). While the slow walking animation will be the same for all participants, in order to choose the speed of the running animation, after the familiarization phase, we will show four different options on the virtual body and individuals verbally report which one is subjectively perceived as considerably fast but feasible. This is necessary to maximize the possibility of having an actual physiological activation but, at the same time, to display an animation that is subjectively plausible so as to not break the illusion of ownership in 1PP.

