### Measurements

#### Heart rate

During the interventions, in order to check if participants actually perceive the virtual body as their own (in 1PP and not in 3PP), we will record the HR with a Polar H10 HR monitor, controlled by a specific application via Bluetooth. Participants have to wear an elastic strip around the chest on which the HR monitor is attached, positioning it close to the heart, in order to record the HR for each intervention conditions (1PP and 3PP) during the baseline (4 min), the intervention (4 min running, 4 min slow walking, for a total of 8 min) plus an extra 30 s (where the participant is still with closed eyes) to check for eventual delay in the recording and to wait for the synchronization of the HR.

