## Discussion

The background of this RCT protocol study starts with two assumptions, based on data presented in the literature: (1) HIE has acute beneficial consequences on executive functions and their neural basis [17, 67]; and (2) the movements of their own virtual body can generate measurable consequences on their real body, comparable to the ones when we actually move [33, 41].

Consequently, we hypothesized that the same HIE intervention performed by their own virtual body (and not by the real participants’ bodies) can have the same beneficial acute effects on executive functions.

In order to confirm our hypothesis, 30 healthy young adults will undergo a vHIE, where the virtual body exclusively (the real body is still sitting) will perform 8 min of training, alternating 30 s of running and 30 s of slow walking; the same vHIE will be performed in two intervention conditions: 1PP, the virtual body will be displayed with the real one, spatially replacing it, and so it will be considered as their own; in 3PP, the virtual body will be displayed 1.5 m away on the right side of the real one, and so it will simply be considered as someone else. During the vHIE, we will record the HR: we predict finding a fluctuating trend of the HR during the intervention in 1PP (and not in 3PP), coherent with the virtual movements, as if the individual is actually performing them. In addition, we will ask the participants to report verbally any subjective feelings during the intervention, predicting that increased sensations of SoBO and SoA in 1PP respect to 3PP will be found.

To test our main hypothesis about acute beneficial effects on executive functions, before and after the two vHIE intervention conditions, we will record the participants’ performance of the Stroop task; at the same time, we will record cortical hemodynamic changes over the PFC with the fNIRS. We predict finding better performance, in terms of reaction time and accuracy, in the Stroop task and higher activation of the neural correlated areas (i.e. PFC) after the vHIE in 1PP (and not after 3PP).

If we confirm our hypothesis, it means that virtual training performed only with the own virtual body can raise the same physical but especially cognitive and neural consequences of a “real” physical one.

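### The heart-rate averaging rule states no lag for 30-s alternating blocks and does not use the 30 s recorded to check for delay, so the running-versus-walking contrast is weakened

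*Protocol article*

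**What the plan says.** The abstract describes the intervention as "eight sets of 30 s of running followed by 30 s of slow walking", and the Interventions section gives the same pattern: "alternating 30 s of running and 30 s of slow walking, for a total of 8 min". The Heart rate section under Measurements splits the recording into a 4-min baseline and an intervention of "4 min running, 4 min slow walking, for a total of 8 min". It adds a further 30 s, with the participant still and eyes closed, "to check for eventual delay in the recording and to wait for the synchronization of the HR".

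Under Statistical analysis, Heart rate data, "the data of the three recording periods (baseline, running, and slow walking) for 4 min each will be averaged". The baseline mean is taken off to give dHRr (running) and dHRw (walking), which enter "an ANOVA 2 × 2 with factor HR speed at two levels" and CONDITION (1PP, 3PP) as the second factor. The stated sign of embodiment is: "We predict finding a significant increase in the dHRr in the 1PP condition, with respect to all the other measurements". The Discussion expects the same time course: "we predict finding a fluctuating trend of the HR during the intervention in 1PP (and not in 3PP), coherent with the virtual movements".

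Neither HR section says how a delay seen in the extra 30 s would enter the running and walking means. The fNIRS data section, by contrast, defines a delayed response window and gives the delay of the signal as the reason.

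**The concern.** HR need not follow a 30-s switch at once. If it lags, part of the response to running falls into the walking blocks, and part of the recovery falls into the running blocks. The two means move towards each other, and so does the comparison of dHRr with dHRw in 1PP. That comparison is one leg of the pattern that the plan treats as physiological confirmation of embodiment. The speed × CONDITION interaction is exposed in the same way.

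HR belongs to the first analysis phase, which checks whether the virtual intervention worked before the Stroop result is interpreted. A weak or null running-versus-walking contrast could be read as missing embodiment when it partly reflects where the windows were cut.

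**Working it through.** **The plan's own figure.** Eight running blocks × 30 s = 240 s = 4 min, and likewise 4 min for walking; 8 × 60 s = 480 s = 8 min. This reproduces the stated split. The 4-min running and walking means can therefore only be pooled 30-s blocks, and the extra 30 s is not among the three averaged periods.

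**Model (assumed).** The protocol gives no delay or time constant for HR, so both are varied. The 1PP response is taken as a unit step that is on during running and off during walking.

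*Pure delay d (0 to 30 s).* Running mean = 1 − d/30 and walking mean = d/30, so the difference = 1 − d/15. For d = 5, 10, 15 and 20 s this gives 0.67, 0.33, 0 and −0.33.

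*Gradual first-order response with time constant τ, repeating cycle.* Running mean = 1 − (τ/30)·tanh(15/τ) and walking mean = (τ/30)·tanh(15/τ). Hence:

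- difference = 1 − 2(τ/30)·tanh(15/τ), which is always positive;
- average of the two means = 0.5, whatever τ is.

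For example, at τ = 15 s: 1 − 2 × 0.5 × tanh(1) = 1 − 0.762 = 0.238.

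The same response was also simulated over the actual 8 min from rest, with and without 5 s of dead time, and with the windows shifted by the best common lag. Shares are of the full step:

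| τ (s) | Closed form | 8 min from rest | With 5 s dead time | Best common shift, no dead time | Average of running and walking, no dead time |
|---|---|---|---|---|---|
| 5 | 0.668 | 0.670 | 0.339 | 0.773 (4 s) | 0.500 |
| 10 | 0.397 | 0.396 | 0.103 | 0.577 (7 s) | 0.499 |
| 15 | 0.238 | 0.234 | −0.007 | 0.439 (9 s) | 0.496 |
| 20 | 0.153 | 0.145 | −0.054 | 0.347 (10 s) | 0.492 |
| 30 | 0.076 | 0.061 | −0.080 | 0.238 (12 s) | 0.483 |

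**What lag does not touch.** Running and walking contribute 4 min each, so the CONDITION main effect compares (dHRr + dHRw)/2, the mean change over the whole 8 min, between 1PP and 3PP. Over all delays of 0–20 s and τ up to 45 s that were tried, this average stays between 0.45 and 0.50 of the step.

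**What the shrinkage could cost (illustration).** Take a two-sided paired t-test at 0.05, n = 30, an assumed standardised running-minus-walking difference of 0.8 without lag, and an unchanged standard deviation. The noncentrality is 0.8 × share × √30. Power is 99% at a share of 1, 40% at 0.40, 10% at 0.15 and 5% at 0.

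**The case against.** The strongest reply is that the planned ANOVA already contains the lag-robust comparison. Its CONDITION main effect is exactly the 1PP-versus-3PP difference in mean HR change over the 8 min. A reader might infer that a real 1PP rise would be reported as absent; the protocol does not support that, because the rise would still appear in this term. Online and offline questionnaires are separate first-phase checks, HR is only an additional outcome, no numerical HR gate is set, and the Stroop ANOVA uses no HR data. All of this stands and confines the point to the speed contrast and the interaction.

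Second, a reader might infer that the plan rules out a lag. It does not: the text is silent on window edges, and the extra recording shows that delay was considered. A condensed article may leave alignment details to a fuller document. That defence is only partial here. The article itself fixes the averaging periods, the difference formulas, the ANOVA and the confirming pattern, and none of them takes up the delay provision made under Measurements.

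Third, the kinetics are assumed. Nothing in the protocol favours a slow response over a fast one in a motionless participant, and at τ = 5 s two thirds of the contrast survives. A reader might also infer that slow response alone can flip the sign; the closed form shows that it cannot.

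**Conclusion.** The point holds as a gap between two sections: a delay is foreseen and recorded for, but the averaging rule does not use it. With unshifted windows and a purely gradual response, the running-minus-walking difference keeps about 67% of the step at τ = 5 s, 40% at 10 s, 24% at 15 s and 8% at 30 s. Disappearance or reversal needs dead time, for example 5 s together with τ of about 15 s or more, or a pure delay of 15 s (null) or longer (reversed). These sizes rest on an assumed first-order response and assumed delays.

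The damage is limited to the running-versus-walking part of the predicted pattern and the speed × CONDITION interaction. The weakness in interpretation is that the plan names the full pattern as confirmation and does not single out the term that survives lag.

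**What to change.** In Heart rate data:

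1. Shift all running and walking windows by one common lag, identical in 1PP and 3PP, either fixed in advance or set from data pooled over both conditions. Fixing it in advance is cleaner, because a lag picked to maximise the running-minus-walking difference makes that difference look larger than it is.
2. Use the extra 30 s to complete the last walking block. That recording is made with eyes closed, but a 12-s lag would draw only 12 of 240 walking seconds (5%) from it.
3. Name the CONDITION main effect already in the planned ANOVA (mean HR change over the 8 min, 1PP versus 3PP) as the lag-robust HR check. State that a null running-versus-walking contrast alone will not be read as absence of embodiment.

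The cost is analysis wording only, since all the data are already planned for recording. The shift restores the sign of the contrast but not its full size when the response is gradual: about 44% at τ = 15 s and 24% at 30 s. That is why the third item is needed as well.

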#### Data from the online and offline questionnaires on SoBO and SoA

As a subjective counterpart, the data from the questionnaires will be analyzed. The online questionnaire will be repeated in five different timepoints (baseline, 1 min, 2.30 min, 5 min, and 6.30 min): to exclude temporal effect, we will first compare the factors TIME (corresponding to the previously mentioned timepoints where the online questionnaire is administered) and QUESTION (corresponding to the four statements of the online questionnaire) with an ANOVA 5 × 4. We can eventually proceed to an average of the statements across timepoints and then we will compare the four statements (specifically comparing results from “real statements” with “control ones”) and the CONDITION (1PP, 3PP) in an ANOVA 4 × 2. We predict finding higher levels of ownership and agency for the real statements in 1PP, in respect to the control statements and in respect to 3PP.

Concerning the offline questionnaire (administered at the end of every IVR condition), we will analyze the data comparing statements among the two conditions (1PP and 3PP).

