These results would contribute on different levels: from a theoretical perspective, this study would be another proof that the illusion of ownership over the virtual body is extremely effective and can be manipulated in order to arise effects on different levels (perhaps motor and cognitive). The simple fact that it is possible to show some effects consequent to the virtual illusion, comparable to the real ones, means the virtual movements are as effective as the actual ones. Our idea is that the SoBO (here the main variable manipulated through the perspective) can drive other aspects, such as motor function, and those, in turn, can drive others, such as cognitive functions. Theoretical models of motor control should clearly state the body and the sense of body ownership as a variable that can significantly affect the resulted action [68, 69].

From a clinical perspective, these results will have interesting applications: as previously mentioned, the intervention presented here can be very useful for sedentary people or those suffering from cardiopathy to start physical activity in a totally safe and entertaining way, or combining cardio or power exercise, and the IVR training, maximizing the efficacy of both on somatic and cognitive terms. In more extreme situations, patients with motor disorders can perform the virtual training but with the same beneficial effects as physical training [70].

However, this study has some limitations. All participants have to repeat the Stroop task four times (before and after the two IVR sessions). This could have a learning effect, or an effect due to the repetition itself, as a negative consequence. To avoid this, we will randomize the order in which the intervention conditions will be administered, but it is still possible to have a repetition effect. Another potential limitation concerns the control conditions of the intervention: several previous studies using IVR exploit the 3PP as a control condition. In some cases, it seems to have a sort of effect, although the reported effect is smaller than the one of the experimental condition. Finally, a difference between the previous study with a similar design and the current one concerns the type of intervention: in Kujach et al. [17], the training consists of a cycling exercise, while in our study we decided on a running exercise in order to be as consistent as possible with other previous studies with similar IVR setup [33].

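### The heart-rate check reads a larger response in 1PP as embodiment in 1PP only, but the planned difference test cannot show that the response is absent in 3PP

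*Protocol article*

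**What the plan says.** The Statistical analysis section sets up two phases. Heart rate and the questionnaires are examined first, to see whether the virtual intervention worked. Stroop and fNIRS come second.

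For heart rate, the Heart rate data section forms dHRr (running minus baseline) and dHRw (walking minus baseline). It analyses them in a 2 × 2 ANOVA of speed by condition. The prediction is: "We predict finding a significant increase in the dHRr in the 1PP condition, with respect to all the other measurements". Its stated purpose is "in order to confirm the physiological counterpart of the embodiment of the virtual body in 1PP only".

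The aim is put the same way elsewhere. The Abstract's Methods paragraph has "To confirm that individuals have the illusion of ownership and agency over the virtual body in 1PP (and not in 3PP". The Heart rate section under Measurements has "in order to check if participants actually perceive the virtual body as their own (in 1PP and not in 3PP". The Discussion predicts that heart rate will follow the virtual movements in 1PP and not in 3PP.

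Two other places are worded differently. The questionnaire analysis is comparative: "We predict finding higher levels of ownership and agency for the real statements in 1PP, in respect to the control statements and in respect to" (the sentence ends by naming the third-person condition). On 3PP as a control condition in earlier studies, the limitations paragraph of the Discussion says: "In some cases, it seems to have a sort of effect, although the reported effect is smaller than the one of the experimental condition".

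**The concern.** *Larger in 1PP* and *in 1PP only* are different conclusions. The first needs a difference between conditions. The second also needs evidence that the 3PP response is nil or negligible. The article names only a difference test, and then attaches the second conclusion to it.

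A partial 3PP response, which the limitations paragraph allows for, would therefore be reported as absence. This matters because the first-phase check is how the rest of the trial is read. If 3PP is declared free of the illusion, the 1PP–3PP contrast will be taken as the whole effect of embodiment. If 3PP carries part of the response, that contrast measures only the difference between a stronger and a weaker illusion.

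**Working it through.** **Plan's own figure.** The article gives no figure for the heart-rate check: no margin, bound or expected 3PP response. Its sample size (28, with 30 recruited) is for Stroop RT, and only the n is used here.

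**Inputs.** From the article: n = 30 recruited, α = 0.05, the four cells of the heart-rate ANOVA, and the prediction that 1PP running exceeds the other three. Assumed, because the article gives none: two-sided tests, the true cell means, SD 1 in each cell, correlation 0.5 between cells, and a reading of the prediction as three paired comparisons that must all be significant.

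**Step 1: what the test addresses.** Write μ for the true mean change in a cell. The prediction concerns μ(1PP run) − μ(1PP walk), μ(1PP run) − μ(3PP run) and μ(1PP run) − μ(3PP walk). None of these is μ(3PP run), and none is μ(3PP run) − μ(3PP walk). All three can be positive whether the 3PP quantities are zero or not.

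**Step 2: how often a partial 3PP response gives the predicted pattern.** Take means of 1.0 (1PP run), 0.3 (1PP walk), 0.4 (3PP run) and 0.1 (3PP walk).
- The SD of a paired difference is √[2 × (1 − 0.5)] = 1, so the standardised differences are 1.0 − 0.3 = 0.7, 1.0 − 0.4 = 0.6 and 1.0 − 0.1 = 0.9.
- The hardest comparison, 0.6, has power 0.888 at n = 30 (noncentral t).
- Over 40,000 simulated trials, all three comparisons succeed in 86.4%.
- In 40.8% of all trials the pattern appears and the 3PP running change is not significant against zero. In the other 86.4 − 40.8 = 45.6% of all trials the pattern appears while the 3PP running change is itself significant.
- With the 3PP running mean at 0.3, the pattern appears in 92.7% of trials, and in 61.0% the 3PP running change is also not significant.

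So the label *1PP only* could be attached to data that visibly contain a 3PP response.

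**Step 3: what n = 30 says about 3PP.** The 95% interval half-width for a within-person mean is t(0.975, 29)/√30 = 2.045/5.477 = 0.373 SD of that quantity. An observed 3PP change of exactly zero would still be compatible with a true change of up to 0.37 SD.

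**Step 4: why a non-significant 3PP result would not fill the gap.** No such test is planned. If someone ran one (two-sided 5%), it would miss a true change as follows.

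| True 3PP change | Missed at n = 30 | Missed at n = 28 |
|---|---|---|
| 0.3 SD | 64% | 67% |
| 0.4 SD | 44% | 47% |
| 0.5 SD | 25% | 28% |

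**Step 5: could absence be shown formally?** Two one-sided 5% tests at n = 30, with a true 3PP change of zero, have power 0.38 for a margin of 0.4 SD, 0.70 for 0.5 SD and 0.88 for 0.6 SD. Only a wide margin is within reach, and the documents give no basis for choosing one.

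**The case against.** The case for leaving the plan alone has several parts.

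- *Heart rate is an additional outcome and the sentence is a prediction.* This is true and limits the severity. But the sentence states what the finding would confirm, and the same aim is repeated in the Abstract and under Measurements.
- *The 86% is not an error rate.* This stands. 1PP really is larger in that scenario, so the figure is close to the power for a true superiority. Only the word *only* would be wrong. The means, correlation and three-comparison reading are all assumptions.
- *The limitation is already disclosed.* The Discussion does admit a possible 3PP effect, but the stated inference was not adjusted to match.
- *A non-zero dHRr in 3PP could be general arousal.* This is fair, and is why running minus walking in 3PP should be shown beside dHRr.
- *Intervals and margins belong in the analysis plan.* Their absence is not the fault here. The article states a test and a conclusion together, and they do not match.

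Two stronger readings are tempting, and the documents do not support them.

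A reader might infer that the trial will also conclude that the cognitive or cortical gain is absent after 3PP, since the Discussion says "after the vHIE in 1PP (and not after 3PP". That is a prediction. Primary outcomes, Secondary outcomes and the Stroop analysis section all define the inference as 1PP against 3PP, which is valid whatever the 3PP effect is. A partial 3PP response would shrink that contrast, not inflate it. This follows from the choice of control, and rewording does not alter it.

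A reader might also infer that absence is to be declared from a non-significant 3PP test. No such test is written, so this is a possible misuse and not a planned step.

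**Conclusion.** The concern holds for the heart-rate and illusion check, at minor severity. The difference test supports *larger in 1PP than in 3PP* and does not support *in 1PP only*. Under the assumed means, a 3PP response 40% the size of the 1PP response would still be given that label in about 86% of trials. The exact rate depends on those assumptions, but the logical gap does not. The half-width of 0.37 SD needs only n = 30 and approximate normality. The primary Stroop comparison, the fNIRS comparison and the sample size are untouched.

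**What to change.** 1. In the Abstract's Methods paragraph, the Heart rate section, the Heart rate data section and the heart-rate sentence of the Discussion, state the conclusion as *larger in 1PP than in 3PP*. The questionnaire analysis already uses this form.
2. Report the 3PP heart-rate response, both as dHRr and as running minus walking, with its 95% confidence interval. State that absence in 3PP is not to be claimed from superiority of 1PP or from a non-significant 3PP result.
3. For consistency with the outcome and Stroop sections, change the Discussion's *and not after 3PP* to *more than after 3PP*.

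Do not add an interval-based rule for declaring absence on the Stroop task. The Discussion says that four administrations may produce a learning or repetition effect, so the before–after change in 3PP mixes practice with any effect of the condition. The planned contrast between conditions removes the practice effect that is common to both.

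The cost is a few words and two intervals from data already being collected. Design, sample size and primary analysis stay as they are. The downside is a weaker statement about 3PP: the trial could no longer say that the illusion is absent there.
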